### **2.2. Secondary Objectives**

1. To compare outcomes between patients in the two study arms, with respect to rates of organ preservation, compliance with the neoadjuvant protocol, and adverse events.
2. To measure patient-reported functional outcomes and quality of life (QoL) in patients with LARC treated with TNT and NOM, and compare them to patients treated with TNT and TME.

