#### **3.2.2.1 Induction neoadjuvant chemotherapy (INCT)**

A number of European studies have investigated the efficacy of INCT in LARC patients treated with CRT, but the results are difficult to interpret due to study heterogeneity.[10, 12, 14-19] In most studies, however, 84% to 97% of patients completed INCT. Additionally, INCT did not impact compliance with CRT or the probability of an R0 resection. Reported rates of pathologic complete response (pCR) ranged from 7% to 29%. Two prospective trials have randomized patients to receive INCT, CRT, and TME, or CRT, TME and ACT. In the larger

trial, all 54 patients in the induction group started INCT and 51 (94%) completed all cycles. In contrast, only 37 of 49 (76%) patients in the adjuvant group started ACT, and only 28 (57%) received all cycles with or without dose reductions. pCR rates were 14% in the INCT group compared to 13% in the ACT group.[10] In another trial comparing INCT and CRT with CRT alone, 96% of patients completed the study per protocol. The pCR rate did not differ between study arms.[19] Unfortunately, the follow-up in most INCT studies has been too short, reporting survival outcomes at 12 or 18 months only, or not reporting them at all. Therefore, the effect of INCT on local recurrence and survival in LARC patients treated with CRT remains unknown.

The group at MSKCC led by [name] has the largest experience in the United States with INCT in LARC. In the MSKCC 07-021 trial, 32 patients with stage II and III rectal cancer were treated with FOLFOX and Avastin. Two patients did not complete treatment due to toxicity, the rest had R0 resections, and 8 (25%) had a pCR. One patient died after surgery.[20] Recently, the group has reported on a series of 44 stage III and IV rectal cancer patients treated with INCT, CRT and TME. Forty-two (95%) completed the treatment per protocol. Some patients with stage IV disease did not undergo TME due to disease progression or patient refusal, but of the 37 who had TME 8 achieved a pCR (22%).[21] These data suggest that INCT is safe in LARC patients, and that most patients completed treatment per protocol.

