## 4.2 Intervention

The neoadjuvant chemotherapy regimen is prescribed specifically as 8 cycles of FOLFOX or 5 cycles of CapeOX over a period of approximately 15-16 weeks. The CRT regimen consists of the standard algorithms: a total of 5400-5600 cGy of radiation (4500 cGy to the pelvis, with an integrated boost to the primary tumor and involved nodes of 500 cGy, followed by an optional 400-600 cGy boost to the primary tumor and involved nodes) delivered in 27-28 fractions, respectively, of 180-200 cGy each over a 5-6 week period. Starting on the first day of RT, patients receive 5-FU administered by continuous infusion or capecitabine for the duration of the radiotherapy.

An interval evaluation will be conducted after completion of INCT in Arm 1, and after completion of CRT in Arm 2. Patients with tumor progression at interval evaluation will be treated according to standard practice as per treating institution guidelines; those with evidence of response or stable disease will complete neoadjuvant therapy. Patients in both arms will be re-staged after completion of all neoadjuvant therapy. Those with a clinical response insufficient to warrant non-operative management safely at the time of re-staging evaluation will undergo a TME. Patients with near complete clinical response or clinical complete response will be treated with NOM. Patients in both arms (TME and NOM) will be followed according to NCCN guidelines. Patients in the NOM group will be evaluated using rectal MRIs and endoscopic exam (see section 10). Patients in the NOM group who undergo subsequent TME will be followed according to current NCCN guidelines.

Pathology assessment of the surgical specimens will be performed according to the College of American Pathologists guidelines. Completeness of the mesorectal excision, tumor regression grade (TRG), and tumor staging will be categorized according to the criteria specified in the current edition of the AJCC Staging Manual.[87]

Safety will be assessed by documenting adverse events during TNT and after surgery. Adverse events will be graded according to NCI CTCAE version 4.0, and surgical complications will be graded according to the Clavien-Dindo classification.[88] Refer to Appendix N to see the classification scale.

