## 9.0 TREATMENT/INTERVENTION PLAN

### 9.1 Neoadjuvant Chemotherapy

There are several variations of the basic FOLFOX regimen. The specific version of the FOLFOX regimen that will be used in this trial is modified, or mFOLFOX6. This entails administration of 5-FU and leucovorin all on day 1 (in contrast to the FOLFOX4 regimen, where this is divided over 2 days) and administration of 85 mg/m^2 of oxaliplatin. Instead of referring to the regimen as mFOLFOX6, we refer to this neoadjuvant regimen, more simply, as FOLFOX.

Patients will receive 8 cycles of FOLFOX, administered every other week. FOLFOX will be given on Day 1 of each cycle. Patients will receive oxaliplatin 85 mg/m^2 IV (over 120 minutes or according to standard institutional guidelines), leucovorin 400 mg/m^2 IV (over 120 minutes or according to standard institutional guidelines), 5-FU 400 mg/m^2 IVP, and 5-FU 1200 mg/m^2/day CIV over 2 days (total dose of 2400 mg/m^2 over 46-48 hours) for a total of 16 weeks/8 cycles.

For patients receiving CapeOX; Oxaliplatin will be delivered at 130 mg/m^2 over two hours day 1 or according to standard institutional guidelines, and capecitabine at 1000mg/m^2 BID days 1-14. They will be repeated on a 21 day cycle, for a total of 15 weeks/5 cycles (maximum total cumulative oxaliplatin dose 650 mg/m^2). To track compliance, patients will be asked to complete a pill diary for each cycle of CapeOX (Appendix G).

In an effort to prevent adverse events, all patients will be treated with anti-emetics and supportive agents as per institutional guidelines. For patients treated outside of MSKCC, supportive and antiemetic agents may be administered per that institution's standard

practices. If the institution does not have a standard practice, then these may be administered at the discretion of the primary oncologist.

The FOLFOX and chemoradiotherapy regimens used in this clinical trial represent the standard care for treatment of patients with locally advanced rectal cancer. Therefore, all clinicians recruiting study subjects have considerable experience with this regimen. The toxicity of each specific agent is outlined below. The regimens used in this clinical trial also represent standard care for patients with locally advanced rectal cancer.

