### **13.0 CRITERIA FOR REMOVAL FROM STUDY**

All patients will be followed for five years from the last date of treatment. Only patients that choose to withdraw consent will be removed from the study and will no longer be followed.

A patient has the right to withdraw from the study at any time for any reason without prejudice to his/her future medical care by the physician or at the institution.

Every effort will be made to evaluate patients for eligibility prior to enrollment. However, if it is discovered that a patient is found to be ineligible after enrollment, the patient will be removed from the study.

Patients may discontinue protocol treatment without being taken off study. Patients who do not complete protocol treatment will remain on study but will be treated at the discretion of their treating physician. Patients placed on the NOM arm who then undergo TME at a later date will remain on study and be followed according to current NCCN guidelines.

If a patient chooses to discontinue treatment, is removed for clinical reasons, and/or received non-protocol treatment, the study team will continue to follow the patient based on intent-to-treat and collect data for up to five years.

Patients may discontinue treatment for any of the following reasons:

1. Unacceptable toxicity, both severe and unexpected
2. Investigator considers it would be in the patient's best interest to not continue
3. Patient is unwilling or unable to continue study treatment
4. Patient becomes pregnant
5. Lost to follow-up

Patients that discontinue protocol treatment must be followed for existing adverse events (AEs) for 30 calendar days after the last day of study treatment. All Grade  $\geq 3$  events considered unexpected and SAEs (as outlined in 17.2) occurring during that period must be reported to the participating site IRB and MSK per section 17.2. These events must be followed up until resolved, unless the condition is unlikely to resolve because of underlying disease, in the treating physician's opinion. After the 30-day period, patients will be followed for disease and survival status for up to 5 years. Limited information about subsequent treatment will be collected and may include chemotherapy, radiation therapy, and clinical exams, and imaging.

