In addition, we will calculate therapy compliance using the following measures: the number of days RT was held, the number of RT delays of  $\geq 1$  week, the number of dose delays and the number of dose reductions in INCT and CNCT. We will also calculate the rate of select hematologic events (as outlined in 17.2), select non-hematologic events (as outlined in 16.0), and unexpected Grade 3 or higher non-hematologic adverse events and surgical complications in each treatment arm. Comparisons will be done using the Wilcoxon Rank Sum test or the Fisher’s Exact test.

**14.3 Secondary objective 2.:** *To measure patient-reported functional outcomes and QoL in patients with LARC treated with NCT, CRT and NOM, and compare these to patients treated with TME.*

The primary analyses for this aim will use data combined across both treatment arms; however, differences according to treatment will also be investigated. The primary endpoint will be QoL as measured one year from the end of TNT. Secondary endpoints will be bowel, sexual, and bladder function. While the subscales will be reported, the primary secondary endpoints will be the total scores on the BFI, FSFI and IIEF. With a total of 325 patients accrued, we expect that 129 patients will obtain complete clinical response and 196 will undergo TME. Approximately 15 to 30 patients initially treated with NOM are expected to cross over to TME at some point during follow-up. For the primary analyses, the NOM group will include these cross-overs on an intent-to-treat analysis. In secondary analysis, patients who eventually crossed over to receive surgery will be included in the TME group. We define this analysis as a comparison between TME vs. durable NOM. Durable NOM is defined as 3-year disease-free survival. We expect that 70% of patients will complete the QoL assessment at 1 year. This response rate takes into account refusals to complete the QoL

questionnaires, and the approximately 20% of patients who will develop distant disease or die before the 1-year time point. Thus, at 1 year we expect to have information on 94 TME patients and 62 NOM patients.

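### Section 14.2 measures neoadjuvant compliance only by holds, delays and dose reductions, so treatment never given is not directly registered and the arm comparison can mislead if completion differs

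*Protocol*

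**What the plan says.** Section 2.2 commits the trial to comparing the arms "with respect to rates of organ preservation, compliance with the neoadjuvant protocol, and adverse events". Section 14.2 turns the compliance part into a definite list: "we will calculate therapy compliance using the following measures: the number of days RT was held", then RT delays of at least one week, then "the number of dose delays and the number of dose reductions in INCT and CNCT". On the analysis it says: "Comparisons will be done using the Wilcoxon Rank Sum test or the" Fisher's exact test. No other section adds starting, completing or dose received to this comparison. Section 14.2 calls the compliance and adverse-event comparisons exploratory.

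The planned exposure is stated in section 4.2: "The neoadjuvant chemotherapy regimen is prescribed specifically as 8 cycles of FOLFOX or 5 cycles of CapeOX". Section 9.1 repeats the CapeOX total: "for a total of 15 weeks/5 cycles". Chemoradiation (CRT) comes second in Arm 1 and chemotherapy comes second in Arm 2.

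The protocol expects some patients not to finish. Section 14.1 allows for about 10% dropping out before the regimen is complete. Section 9.3.1 sends patients with progression at the interval evaluation to institutional standard practice. Section 13.0 lists reasons for discontinuing and states: "Patients who do not complete protocol treatment will remain on study but will be treated at the discretion of their treating physician".

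**The concern.** Each listed measure is an event count that mostly accrues while treatment is being given. Stopping removes the opportunity for further events. Someone who stops after one uneventful cycle has no delays and no reductions, and so ranks ahead of someone who finishes all eight FOLFOX cycles with one delay.

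This matters because section 3.2.2 argues for chemotherapy before surgery partly on the ground that more patients will receive it, and the background relies largely on start and completion rates. Section 3.2.2.1 reports: "In most studies, however, 84% to 97% of patients completed INCT". The measures in 14.2 cannot produce a figure to set beside that one.

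The component at risk of omission also differs by arm. Leaving between the two halves removes RT counts in Arm 1 and chemotherapy counts in Arm 2, so the gap need not cancel.

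**Working it through.** The protocol gives no rate, power or sample size for compliance, so there is no figure to reproduce. The check has three parts.

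**1. What each measure can register.**

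| Measure in 14.2 | Accrues when | Registers treatment never given? |
|---|---|---|
| Days RT held | RT is under way | Not directly |
| RT delays of at least 1 week | RT is under way or scheduled | Not directly |
| Dose delays | A cycle is due | Not after stopping |
| Dose reductions | A cycle is given | Not after stopping |

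**2. What the background reports.** Induction: 84% to 97% completed, so 100 − 97 = 3% to 100 − 84 = 16% did not. In the larger randomised induction trial, 51 of 54 = 94% completed. In its adjuvant group, 37 of 49 = 76% started and 28 of 49 = 57% received all cycles. In the small consolidation series, 28 of 29 = 97% completed. The 80% from the larger consolidation trial is completion *without interruption*, a mixed measure, so its complement is not a non-completion rate.

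**3. Size, under assumed rates.** Group size: 325 / 2 ≈ 162 per arm. Let *u* be the chance of never starting chemotherapy, *s* the chance of stopping after each cycle, and *d* the chance of a delay per cycle, with 8 cycles and non-starters scored zero. Then:

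- completion = (1 − u)(1 − s)^7
- mean cycles = (1 − u)[1 − (1 − s)^8] / s
- mean delays = d × mean cycles

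Arm A (u = 0, s = 0.0088, d = 0.15): completion 0.9912^7 = 94%; mean cycles 7.76; mean delays 1.16.

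| Arm B: u, s, d | Completion | Mean cycles | Mean delays | Wilcoxon significantly favours B | Favours A |
|---|---|---|---|---|---|
| 0, 0.0088, 0.15 | 94% | 7.76 | 1.16 | 2.5% | 1.5% |
| 0.05, 0.02, 0.15 | 82% | 7.09 | 1.06 | 18% | 0.1% |
| 0.10, 0.03, 0.15 | 73% | 6.49 | 0.97 | 43% | 0% |
| 0.15, 0.05, 0.15 | 59% | 5.72 | 0.86 | 87% | 0% |
| 0.15, 0.05, 0.18 | 59% | 5.72 | 1.03 | 33% | 0.1% |

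The last two columns come from 1,000 simulated trials per row. Fisher's exact test on completion (200 trials per row) was significant in about 89% of runs at 94% versus 82%, and in essentially all runs in the rows below that.

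*If non-starters are missing rather than zero*, the factor (1 − u) drops out. For *d* = 0.15, arm B's mean delays become 0.15 × 7.46 = 1.12, 0.15 × 7.21 = 1.08 and 0.15 × 6.73 = 1.01, against 1.16 in arm A. The direction is the same and the difference is smaller.

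*Equal dropout need not balance each measure.* Suppose 10% of each arm leaves between the halves, everyone else finishes, and an unstarted component scores zero. With eight cycles and *d* = 0.15, mean chemotherapy delays are 8 × 0.15 = 1.20 in Arm 1 and 0.9 × 1.20 = 1.08 in Arm 2. RT counts fall by the same tenth in Arm 1.

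**The case against.** Several points on the other side stand.

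- Zero scoring of an unstarted component is an assumption. Non-starters could be treated as not evaluable, and the statistical analysis plan, which is not at hand, may settle this.
- Early stoppers keep the delays and reductions already counted. A reader might infer that they score as fully compliant. That is exact only for someone with no event before stopping, or for an unstarted component if it scores zero.
- RT stopped early could register if the remaining planned days are counted as held (section 11.7.1). Dropping oxaliplatin could register as a reduction, because the lowest dose level in the FOLFOX table in section 11.7.2 is 0.
- The simulation makes delay independent of stopping. Section 13.0 lists toxicity as a reason to stop, so stoppers may carry more earlier delays, which would shrink the effect.
- With equal chemotherapy completion there was no systematic direction: about 4% of runs were significant, split both ways. The protocol gives no basis for expecting gaps as wide as 94% versus 59%.
- A reader might infer that eight FOLFOX against five CapeOX cycles biases the comparison. Either regimen is allowed in both arms and randomisation is stratified by institution, so this adds noise rather than direction.
- A reader might also infer that every cited study reports compliance as completion. Section 3.2.2 also cites planned dose received without delay, and one consolidation figure is completion without interruption.

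Exploratory status and the existing treatment records limit the consequence, since completion could still be reported descriptively. Neither changes the fact that the protocol names the compliance measures and leaves completion off the list.

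**Conclusion.** The point holds as a weakness in how one exploratory secondary outcome is defined. The listed counts do not directly register treatment never given and are not scaled to treatment received. If completion differs between arms, the comparison can mislead and may favour the arm with more early stopping.

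The size cannot be fixed from the protocol. Under the assumed rates, the worse arm was significantly favoured in 18% of runs for a 12-point completion gap (94 − 82) and in 43% for a 21-point gap (94 − 73). These figures show direction and are not forecasts. They rest on equal delay rates, on delay being unrelated to stopping, and on non-starters scoring zero. A higher delay rate in the worse arm weakens the effect: at 59% completion, raising the chance per cycle from 15% to 18% cut the figure from 87% to 33%.

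A reader might infer that the comparison will point the wrong way, or that the trial cannot address this objective. The documents support neither. Reversal needs unequal completion of the component being measured, and the data for a better measure exist. The 3-year disease-free survival analysis and the pick-the-winner rule, which counts patients under non-operative management, do not use these measures.

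**What to change.** In section 14.2 add, by arm and in all randomised patients:

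- **Start and completion.** The proportion starting and the proportion completing each component: 8 FOLFOX or 5 CapeOX cycles, and the planned RT course, with the optional boost counted only where prescribed. Count never-started as not completed and tabulate the reasons. Show exits for progression at the interval evaluation separately from other non-completion, because the protocol itself directs those exits and they reflect disease course rather than adherence.
- **Dose received.** The percentage of planned chemotherapy and RT dose received, set to 0 if not started.

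Keep delays and reductions as supporting measures, reported per cycle started among patients who started that component.

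The cost is wording and a little more analysis. Flow sheets, pill diaries and RT records are already submitted under sections 9.1.1, 9.2.5, 9.2.6.1 and 16.0.1, and treatment and radiation forms are listed in 16.0.2. No treatment, visit or sample size changes.

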## **12.0 CRITERIA FOR THERAPEUTIC RESPONSE/OUTCOME ASSESSMENT**

The primary objective of this study, 3-year DFS, will be assessed on the basis of surveillance procto/sigmoidoscopy, physical examination, and follow-up radiologic scans. For patients who receive TME or NOM, follow-up scans will occur according to current NCCN guidelines for rectal cancer surveillance. Patients in the NOM group will be evaluated using rectal MRI and endoscopic exam (section 10). Patients in the NOM group who undergo subsequent TME will be followed according to current NCCN guidelines. 3-year DFS will be defined as the percentage of patients alive without recurrence of disease at 3 years measured from the date of randomization. Patients in the NOM protocol who develop relapse at the site of the primary tumor but undergo curative TME with negative resection margins will not be counted as having recurrence. However, any patients developing local recurrence after TME, performed either immediately after neoadjuvant therapy or after a period of NOM, will be counted as having recurrence. Scans will be reviewed at MSKCC to resolve any discrepancies in interpretation. Scans showing equivocal evidence of local recurrence will be evaluated with additional imaging as necessary. Biopsy confirmation of local recurrence will be indicated for the purposes of the protocol. Isolated elevation of CEA, in the absence of other evidence of recurrent disease, will not be considered indicative of either local or systemic relapse. Symptomatic evidence of local recurrence will be corroborated on the basis of imaging and/or physical examination. Distant recurrence will also be assessed using follow-up CT scans of the chest, abdomen and pelvis. The MSKCC radiologist will review scans to resolve any discrepancies in interpretation. Central radiology review at MSKCC will review all incoming images and reports, but will only submit feedback on cases in which scans must be repeated or, in the case of interval or re-staging evaluations, where progression is identified in disagreement with the site investigator's assessment. Scans with equivocal evidence of distant recurrence will be evaluated via additional imaging, as

necessary. Biopsy confirmation of distant recurrence will be indicated for the purposes of the protocol.

Adverse events associated with CT and RT-CT will be assessed using the standard criteria described in section 11.0.

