The primary endpoint of QoL will be assessed using the EQ-5D index, an overall measure of QoL and health ranging from 0 (worst health) to 1 (best health). Comparison will be done using the two-sample t-test. The minimally important difference (MID) for 534 cancer patients in the United States has been estimated to be in the range of .05 to .09 when using ECOG performance status as an anchor (Pickard, Neary, Cella 2007). The standard deviation of the EQ-index was .15 in this patient population. With our sample size of 156, we will be able to detect a difference of .07 with 80% power and type I error of 5%, assuming a standard deviation of .15.

In secondary analyses we will use a t-test to compare the EQ-5D index, measured at 1 year, in patients with durable NOM vs. TME. The differences in EQ-5D index from 1 year to 3 years will also be compared in patients with durable NOM vs TME, using an ANCOVA model that adjusts for variables found to be significantly different by NOM vs TME. Trends in the EQ-5D from baseline, 12, 24, and 36 months will be graphed, and evaluated descriptively.

Similar analyses will be done to study all other patient-reported functional and QoL endpoint.

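### Section 14.3 compares 1-year EQ-5D between NOM patients selected for being disease-free at 3 years and a TME group with no such condition, and group membership is not uniquely defined

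*Protocol*

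**What the plan says.** Section 14.3 sets two groupings for the comparison of NOM with TME on quality of life.

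- **Primary analysis.** "For the primary analyses, the NOM group will include these cross-overs on an intent-to-treat analysis". The endpoint is timed from the end of neoadjuvant treatment: "The primary endpoint will be QoL as measured one year from the end of TNT".
- **Secondary analysis.** "In secondary analysis, patients who eventually crossed over to receive surgery will be included in the TME group". No limit is set on when the cross-over happened. The NOM side then becomes durable NOM: "Durable NOM is defined as 3-year disease-free survival". No disease-free condition is stated for TME.

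The test is also fixed: "In secondary analyses we will use a t-test to compare the EQ-5D index, measured at 1 year, in patients with durable NOM vs. TME". The same two groups are used for the 1-to-3-year change in EQ-5D, by ANCOVA. Section 14.3 extends similar analyses to the other patient-reported endpoints.

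Two other sections bear on this. Section 12.0 measures 3-year DFS from randomization and says that NOM patients who "relapse at the site of the primary tumor but undergo curative TME with negative resection margins will not be counted as having recurrence". Section 9.6 restarts the survey cycle after surgery for a NOM patient who later has TME.

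**The concern.** An outcome measured at 1 year is compared between groups that are settled only later. Patients who will relapse or die by 3 years are removed from the NOM side and kept on the TME side. If such patients already feel worse at 1 year, NOM looks better even when surgery has no effect on quality of life.

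There are two further problems. A NOM patient operated on after the 1-year survey is labelled TME for a score given with the rectum in place. And the definitions do not assign every patient to exactly one group, so two programmers could build different data sets from the same text.

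NOM against TME on function and quality of life is secondary objective 2, and section 3.4 says these data are to inform patients' decisions. A contrast whose direction partly reflects how its groups were chosen serves that purpose poorly.

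**Working it through.** **Inputs from the protocol.** Section 14.3: 129 NOM and 196 TME patients; 15 to 30 cross-overs; 94 TME and 62 NOM patients with 1-year data; SD .15; detectable difference .07 at 80% power and 5% type I error; MID .05 to .09; about 20% with distant disease or death before 1 year. Section 14.1: 3-year DFS of 75% and 85%, so 25% and 15% have an event by 3 years.

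**Assumed, not in the documents.** Patients with a later DFS event score d = .05 to .15 lower at 1 year.

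**1. The plan's own figure.** SE = .15 × √(1/94 + 1/62) = .0245. Power for .07 = Φ(.07/.0245 − 1.96) = about .81. The stated 80% is reproduced. It belongs to the primary comparison; no power is stated for durable NOM against TME.

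**2. Selection bias with no true effect.** Durable NOM contains no patients with an event by 3 years, and TME contains a share f. The expected difference in favour of NOM is f × d.

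| Share f of TME responders with a later event | d = .05 | d = .15 |
|---|---|---|
| 0 (85% DFS; 20% before 1 year already exceeds the 15%) | 0 | 0 |
| (25 − 20)/80 = .0625 (75% DFS, early events absent from the survey) | .003 | .009 |
| .15 (85% DFS, no early losses removed) | .008 | .023 |
| .25 (75% DFS, no early losses removed) | .013 | .038 |

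The first two rows take section 14.3 at its word that the 70% completion rate already allows for the roughly 20% with early distant disease or death. The last two apply the full 3-year event share to the TME responders. Against the lower MID of .05, the extremes are .009/.05, just under a fifth, and .038/.05, about three quarters.

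**3. Relabelled cross-overs.** They make up 15/(196 + 15) = 7% to 30/(196 + 30) = 13% of the enlarged TME group, given equal survey response. Suppose TME truly lowers the score by s and all cross-overs are operated on after the survey. The difference seen is then s × 196/(196 + c). For s = .07 this is .065 with c = 15 and .061 with c = 30. This part works against NOM. The documents do not say how many cross-overs come after the survey, so this is the largest dilution for those counts.

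**4. Both together.** If cross-overs have no deficit of their own, the net distortion is (196·f·d − c·s)/(196 + c).
- f = .15, d = .05, c = 30, s = .09: (1.47 − 2.70)/226 = −.005.
- f = .25, d = .15, c = 15, s = .05: (7.35 − .75)/211 = +.031.

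The net sign is not fixed by the design.

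**5. Membership, from the text alone.**

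| NOM patient | By the durable NOM definition | By the cross-over sentence |
|---|---|---|
| Regrowth, margin-negative TME, disease-free at 3 years (not a recurrence under 12.0) | Durable NOM | TME |
| Distant relapse, no TME | Not durable NOM | Not TME |
| Operated on after the 1-year survey | Depends on DFS | TME, with a score from before surgery |

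Because section 9.6 restarts the survey cycle after surgery, it is also open which survey is a cross-over's 1-year score: the one timed from the end of TNT or the one timed from surgery.

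**The case against.** The strongest reply is that this is a secondary analysis of a secondary objective. The primary quality-of-life comparison keeps cross-overs in NOM and is the one with a power statement. That stands: nothing here touches it.

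A second reply is that 15% to 25% is the wrong event share, since section 14.3 expects about a fifth of patients to have distant disease or die before the 1-year point. This also stands, and is why the range starts at zero. It does not make zero the answer. The protocol gives no event rate for TME patients, who are the incomplete responders, and a 20% early event rate cannot be squared with its own 85% target at 3 years.

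A third reply is that, read in order, section 14.3 moves cross-overs to TME before durable NOM is defined, so a salvaged patient is already TME. That is a reasonable reading, but the definition itself rests on DFS alone and does not mention surgery. The patient with distant relapse and no TME remains unassigned on either reading.

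A reader might infer that the whole construction favours NOM, including the transfer of cross-overs. The documents do not support that. Late cross-overs bring scores from before surgery into TME, which narrows a true gap. A reader might also take three quarters of the MID as the expected bias. It needs the highest event share and the highest assumed deficit together.

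**Conclusion.** The concern holds for the secondary durable NOM comparison. Selecting only one side on a later outcome biases the 1-year contrast towards NOM, provided that patients with later events already score lower at 1 year. That deficit is an assumption. For .05 to .15, the bias is about 0 to .009 if patients with early events are mostly missing from the survey, and up to about .04 if 15% to 25% of TME responders have a later event. The relabelling of late cross-overs is a separate fault that dilutes a true difference, so the net direction is not certain. The overlap and the gap in membership, and the unclear choice of survey, need no assumed figures. Because the protocol states the groups, endpoint and test, this is a rule to correct and not a detail left open. It should be corrected, but it does not threaten the primary quality-of-life result.

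**What to change.** Amend section 14.3 as follows.

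- **1-year comparison.** Classify every responder by whether TME had been done by the date of the survey timed one year from the end of TNT, using no later outcome. State that this survey, not the cycle restarted after surgery under section 9.6, supplies a cross-over's score. Give the window to use when the restart leaves no survey near that date.
- **1-to-3-year change.** Require patients in both groups to be alive and disease-free at 3 years. Define durable NOM as meeting that condition and also having had no TME by then.
- **Label.** Call these contrasts descriptive.

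The cost is a wording change to the protocol; surgery reports and surveys are already collected. A limit remains: NOM patients who fail early and are operated on before the survey still count as TME, so the groups stay non-randomised and a difference cannot be read as the effect of surgery.
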